### **Serious Adverse Events and Serious Adverse Device Effects**

For **all serious** AEs, regardless of causality (i.e. both SAEs and SADEs), the investigator must:

- Complete an SAE report.
- Forward the AE and SAE reports, along with relevant supporting documents, to Wellspect HealthCare immediately but no later than the end of the next business day.
- If requested by Wellspect HealthCare, promptly follow up the initial SAE information with a detailed written report.

**NB!** If the cause of death is reported as “unknown” the investigator must actively seek the

cause of death. If an autopsy has been performed, a copy of the results should be obtained (with translation of important parts into English).

- Inform the Ethics Committee of SAEs, as per local requirements (may include both those SAEs occurring at the study site as well as at other participating study sites, as well as cases when the opinion on seriousness/causality differs between him/her and Wellspect HealthCare.)

### Device Deficiencies

The investigator is responsible for recording the following in the CRF for **all** device deficiencies:

- Device deficiency details
- *Start and stop* date, and
- Whether the device deficiency led to an adverse event

For **device deficiencies that fulfil the SADE definition** (see section 6.3.1.1 Serious Adverse Device Effect), the investigator must:

- Complete an extended Device Deficiency (SADE (Potential SAE)) report.
- Forward the Device Deficiency report, along with relevant supporting documents, to Wellspect HealthCare immediately but no later than the end of the next business day.
- If requested by Wellspect HealthCare, promptly follow up the initial information with a detailed written report.
- Inform the Ethics Committee of SADE (Potential SAE), as per local requirements (may include both those SADEs occurring at the study site as well as at other participating study sites, as well as cases when the opinion on seriousness/causality differs between him/her and Wellspect HealthCare.)

## 6.4 Patient-Reported Outcomes (PROs)

### 6.4.1 The Neurogenic Bowel Dysfunction score

To evaluate the effect of Navina System, a patient friendly version of the validated standardized NBD score  questionnaire will be used. The NBD score is a symptom-based score for neurogenic bowel dysfunction that takes into account both constipation and faecal incontinence, and weighs each symptom of NBD according to its impact on QoL in persons with spinal cord injury. The NBD score has a 10-item symptom severity scale to measure the parameters, faecal incontinence, constipation and obstructed defecation.

Each item is assigned a score based on odds ratios for associations between items and impact on QoL. Negative changes in NBD score correspond to an improvement in bowel-related symptoms, and the total NBD score can range from 0 (very minor bowel dysfunction) to 47 (severe bowel dysfunction).

The NBD score is self-administrated and will be completed by all subjects at baseline (visit 1), at 3 months follow-up (visit 2), in connection to the 6 and 9 months telephone follow-ups and at 12 months follow-up (Visit 3) or at end of the treatment period for those subjects with early withdrawal from the study. The subject will be provided with personal log-in details to *Viedoc™Me*, the patient interface of the eCRF, which will be used to complete the NBD score at baseline. The NBD score at 3, 6, 9 and 12 months follow-up will be completed using the Navina Smart app (see further instructions in 5.1.2). If, at any time during the study and for any reason,

the subject is unable to complete web-based questionnaires, the subject will be provided a paper questionnaire. Study site personnel will then enter the data into the study data base.

Applicable scores and results from the questionnaire will be analysed and presented according to the user instructions from the provider. The results from the NBD score at baseline and at the 3, 6, 9 and 12 months follow-up will be compared.

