## 5.1.2 Navina Smart app and compatible mobile devices

### 5.1.2.1 Navina Smart app

Wellspect HealthCare is developing an application – the Navina Smart app (the App) – for mobile devices to be used together with the Navina Smart system. The App is developed as a native app, one for iOS and one for Android, distributed for free via AppStore and Google Play and will be CE-marked at time of study start. Usage of the App requires access to a Navina Smart system unit. The App collects irrigation data from the Navina Smart system via a function in the App called “Synchronize”. Data is transferred to the App from the ECU via Bluetooth technique. Once stored in the App, the irrigations can be rated as well as analysed in the report module. The App also offers functionality for the user to make bowel management evaluations, e.g. NBD Score, and to generate reports.

The App is intended to help Navina Smart users to fine tune their therapy settings in a timely manner, by sharing their irrigation data with a health care professional. This can be done by sending reports as attachments in an e-mail or by showing the App in a meeting with the healthcare professional.

The App is indicated for users of the Navina Smart system. In this study it is mandatory for the subjects to use the App.

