### 8.1 Electronic Data Capture

Data Entry into a central database will be made using Electronic Data Capture (EDC).

Data Entry will mainly be performed by the subjects, but will be performed by study site personnel in cases where EDC is not possible for the subject, *i.e.* where questionnaires are completed using pen and paper (e.g. all EQ-5D-3L forms), for Screening and Demographic variables as well as for AEs and Concomitant Medication.

Data will be entered into eCRFs using Viedoc, a web based EDC system used by WHC. Trained and authorized study site personnel will be responsible for entering data into Viedoc. Data entered into Viedoc will be immediately saved to a central database, hosted by a 3rd party, Pharma Consulting Group Solutions AB.

Study site personnel will enrol subjects using Viedoc. Upon enrolment in the study each subject will be automatically allocated a specific Subject ID (Enrolment number). This is the only identifier used on any study data and the key (the Subject Enrolment and Identification Log) connecting a specific subject to his/her Subject ID will be kept by the Investigator in the Investigator's Study File which is stored securely at the study site.

Subjects will use a site-specific tablet computer to self-report ePRO data using ViedocMe. ViedocMe is the patient interface application of the eCRF and subject specific log-in details will be provided to the subject by site personnel. Upon completion of an ePRO the data will be automatically entered into Viedoc and thus stored in the central database.

The EQ-5D forms will be completed in paper by the subjects.

Subjects unable to complete ePRO will use pen and paper instead. If pen and paper are used, trained authorized study site personnel will enter the data into Viedoc.

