#### 8.1.1 Navina Smart App Data

The Navina Smart app is running locally on the mobile device and all data associated with the App is stored on a local database. No transferring of data to an external database for central storage is performed, except for anonymous data that is stored for the purpose of data analytics in order to improve the product and the therapy. The App may run without Internet connectivity, even though the creation and sending of reports require internet access.

The Navina Smart app communicates with the Navina Smart unit via Bluetooth Smart protocol, and a checksum is used to validate the correctness of the data transferred. The App has no limits of number of irrigation data to be stored, other than the capacity of the mobile device storage.

The Navina Smart app and its data will stay on the mobile device regardless of the user upgrading the App or the operating system. At deletion of the Navina Smart app, data is deleted, except from anonymous data transferred to Wellspect HealthCare.

Reports sent by email from an App user to site personnel will consist of .pdf and .csv files. The email with the attached reports will automatically contain the Subject ID. The .csv files contain irrigation data and NBD Score data and will be uploaded by site personnel into the subject's eCRF.

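### The planned NBD score changes from ViedocMe at baseline to the device's own app at follow-up, so a mode shift cannot be told apart from the device effect on the primary endpoint

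*Protocol*

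**What the plan says.** Section 6.4.1 names two electronic routes for the same questionnaire. ViedocMe is "the patient interface of the eCRF, which will be used to complete the NBD score at baseline". For all later time points, "The NBD score at 3, 6, 9 and 12 months follow-up will be completed using the Navina Smart app". The primary objective (section 2.1 and Table 6) is the change between baseline and 3 months, so one score in each pair is planned by each route.

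The two routes differ in setting and data path. Section 8.1 says: "Subjects will use a site-specific tablet computer to self-report ePRO data using ViedocMe". The app runs on the subject's own phone or tablet, or on a loaned smartphone (section 5.1.2.2). Its scores reach the database through an emailed report; under section 8.1.1, "The .csv files contain irrigation data and NBD Score data and will be uploaded by site personnel" into the eCRF. Section 5.1.2.1 adds "In this study it is mandatory for the subjects to use the App" and "Usage of the App requires access to a Navina Smart system unit".

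There are safeguards. Section 6.4.1 provides that if "the subject is unable to complete web-based questionnaires, the subject will be provided a paper questionnaire", and it requires an NBD score "at end of the treatment period for those subjects with early withdrawal from the study". Section 4.5.2 asks subjects who discontinue for relevant PROs, and for return of devices where possible.

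**The concern.** Section 3.3 attributes any change in NBD score to the device and concludes that no control group is needed. That argument needs the measurement to stay the same while the treatment changes. Here the planned mode changes at the point where treatment starts. If layout, wording, screen or setting moves the answers at all, the movement goes wholly into the baseline-to-3-month change.

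A later analysis plan cannot repair this. No subject is planned to answer by both routes at one time point, and no untreated group switches route, so the data carry no information on the mode effect.

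The study is sensitive to small shifts because section 7.4 aims at a difference of only about 0.8 points on a 0 to 47 scale. A lesser concern is that the default follow-up route runs through the device's app. It is therefore tied to the equipment that subjects who stop are asked to hand back.

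**Working it through.** **Inputs from section 7.4:** two-sided 5% level (Z = 1.96), 90% power (Z = 1.28), difference 0.8, SD of the paired difference 2.2, 80 evaluable subjects.

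**The plan's own figure.** N = (1.96 + 1.28)² × 2.2² / 0.8² = 10.4976 × 4.84 / 0.64 = 79.4, rounded up to 80. The figure is reproduced.

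**Smallest mean change that reaches significance.** 1.96 × 2.2 / √80 = 0.48 points, about 1% of the scale range (0.48 / 47).

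**Rejection rate from a mode shift alone.** Suppose the device has no effect and the switch moves the mean by m. With SE = SD / √80, the probability that the two-sided 5% test rejects is Φ(m/SE − 1.96) + Φ(−m/SE − 1.96). The protocol gives no value for m, so 0.4 (half the target difference) and 0.8 (equal to it) are assumptions.

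| SD of change | SE at n = 80 | m = 0.4 | m = 0.8 |
|---|---|---|---|
| 2.2 (protocol) | 0.246 | 37% | 90% |
| 4.5 (assumed) | 0.503 | 12.5% | 36% |
| 6.8 (assumed) | 0.760 | 8% | 18% |

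For example, with m = 0.4 and SD 2.2, m/SE = 0.4 / 0.246 = 1.626. This gives Φ(−0.334) + Φ(−3.586) = 0.369. The 90% entry is simply the design power, because a shift of 0.8 looks to the test exactly like the effect it was sized to find.

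The larger SDs are shown because the interval cited in section 7.4 (−6.6 to −2.4) has a half-width of 2.1 and hence a standard error of 2.1 / 1.96 = 1.07. The SD of individual changes is that value times the square root of the cited study's sample size, which the protocol does not give.

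These are normal approximations. Section 7.3 plans a Wilcoxon signed rank test, so the percentages are indicative. A larger SD lowers the rejection rate, but the bias in the estimated mean change stays equal to m whatever the SD or sample size.

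**Capture after stopping.** No arithmetic applies, so the provisions are compared:

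- The app needs access to a unit (5.1.2.1), and units are returned where possible (4.5.2). This makes the default route harder to use after stopping.
- Paper is offered (6.4.1), but its trigger is being unable to complete web-based forms. Stopping the device is not named as a trigger.
- A score is due at early withdrawal (6.4.1), but at the end of that subject's treatment. It need not fall at month 3, where the primary endpoint is defined.

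**The case against.** The strongest reply is that no difference between the two versions has been shown. Both are self-administered electronic forms, and the protocol refers throughout to one patient-friendly version of the score. Any shift could be zero or could work against the device. The 0.4 points are hypothetical, and are about 9% of the mean change of 4.5 points that section 7.4 cites for transanal irrigation (0.4 / 4.5). All of this stands as a limit on size: the point is a bias that the design cannot exclude, and no bias has been demonstrated. If the true effect were near 4.5 points, a small shift would hardly alter the test result, though it would still enter the estimate.

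A reader might go further and infer three things that the documents do not support.

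- **That the endpoint is lost, or nearly so, in subjects who stop.** Paper, the early-withdrawal score and the PRO request at discontinuation keep it obtainable. The protocol says that use of the app needs a unit; it does not say that the NBD form is locked once the unit is returned. What remains is a matter of timing and of a loosely worded paper trigger.
- **That every follow-up score comes from the app.** The app is the planned route, and paper can replace it. A paper follow-up after a ViedocMe baseline is still a change of mode.
- **That subjects will answer more favourably in the app to please the therapist.** ViedocMe answers are given on a site tablet and enter the same eCRF, so this is not shown to be a mode effect, and a change of interface would not clearly remove it.

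**Conclusion.** The point holds as a design weakness. The planned mode switch coincides with the start of treatment, there is no control arm and no described equivalence check, and the resulting shift, if any, cannot be estimated from the data. Its size and direction are unknown.

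The 37% figure (assumed shift 0.4, n = 80, SD 2.2) shows how little shift is needed under the protocol's own inputs. It falls to 12.5% and 8% under the assumed SDs of 4.5 and 6.8. The sample size is unaffected. The dependence of the default route on a unit is secondary, and mainly concerns whether a score exists at month 3. The change is worth making because it costs little and cannot be replaced by analysis afterwards.

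**What to change.** Amend sections 6.4.1, 5.1.2 and 8.1.1 as follows.

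- Collect the study NBD score in ViedocMe, with identical wording, at baseline, Visit 2 (3 months) and Visit 3 (12 months). Section 6.4.4 already has subjects complete the Follow-up Questionnaire there at both follow-up visits, with personal log-ins, so the score can be added to the same sitting.
- At months 6 and 9, which are telephone contacts, use the personal ViedocMe log-in if off-site access is confirmed; section 8.1 describes only a site tablet. If it is not available, keep the app for these secondary time points and report the mode of each score.
- Keep the app's NBD function as a clinical tool, and state that it is not the source of the primary endpoint.

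Do not add a second baseline score in the app. A baseline score of at least 10 is an inclusion criterion (section 4.2), so two baseline scores would leave open which one decides eligibility and which one enters the change.

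The cost is a form-schedule change, revised wording and possibly a web log-in at months 6 and 9. For the primary endpoint the email and file-upload step disappears, and the default route no longer depends on a unit. The change of mode does not by itself set the timing of the score in subjects who withdraw before month 3.

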#### 6.4.2 The EQ-5D-3L

EQ-5D is a standardized health-related quality of life questionnaire developed by the EuroQoL Group in order to provide a simple, generic measure of health for clinical and economic appraisal (EuroQoL Group, 1990). The five dimensions questionnaire (EQ-5D) is one of the most commonly used generic questionnaires to measure health-related quality of life (HRQOL). The EQ-5D is short, easy to use and flexible. It consists of a questionnaire and a visual analogue scale (VAS), i.e. EQ-VAS. The EQ-VAS is a self-rated health status using a VAS. The EQ-VAS records the subject's perceptions of their own current overall health and can be used to monitor changes with time. The questionnaire is a self-reported description of the subject's current health in 5 dimensions; *mobility, self-care, usual activities, pain/discomfort* and *anxiety/depression*. The subject is asked to grade their own current level of function in each dimension on a three-graded scale (i.e. no problems, some problems or severe problems). The combination of these creates a unique health state. Each health state can be ranked and transformed into a single score called the utility score, which can be used to estimate QALYs (Quality Adjusted Life Years) in health economic analyses. Due to its universality across diseases and patient populations, EQ-5D is one of the preferred methods to generate utilities for QALY estimation.

The EQ-5D-3L will be completed by all subjects at Baseline (visit 1), at the 3-months follow-up (visit 2) and at 12-months follow-up (Visit 3) or at end of the treatment period for those subjects with early withdrawal from the study. The subject will be provided with a paper questionnaire to be completed and the study site personnel will then enter the data into the eCRF.

Applicable scores and results from the questionnaire will be analysed and presented according to the user instructions from the provider (EuroQoL Group). The results from the EQ-5D-3L at Baseline, 3-months follow-up and 12-months follow-up will be compared as well as the change between the three assessments. The change in utility scores from baseline and the 3-months and 12 months follow-up, respectively, will be used for QALY calculations in health economic analyses.

#### 6.4.3 The “Baseline Questionnaire”

The “Baseline Questionnaire” is a study-specific, non-validated instrument and is developed by WHC to provide measures of current bowel management, bowel dysfunction and frequency of UTI.

The “Baseline-Questionnaire” is self-administrated and will be completed by each subject only at Baseline (Visit 1). The subject will be provided with personal log-in details to *ViedocMe*, the patient interface of the eCRF, which will be used to complete the “Baseline Questionnaire”. If, at any time during the study and for any reason, the subject is unable to complete web-based questionnaires, the subject will be provided with a paper questionnaire. Study site personnel will then enter the data into the study data base.

Applicable scores and results from the questionnaire will be analysed and presented using descriptive statistics.

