## Objectives

The overall objective of the study is to evaluate change in neurogenic bowel dysfunction (NBD) symptoms after use of the Navina™ Smart system. The assumption is that NBD symptoms are constant over time (i.e. 12 months of study duration) and the hypothesis is that any change should be because of the use of the Navina Smart system.

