Usually, a thorough medical examination to exclude other pathologies and to map out the present degree of neurogenic bowel dysfunction is undertaken. This examination should at least consist of acquisition of a careful medical history, a digital rectal examination, physical and neurological examination, functional assessment and a radiological examination. The use of specific disease severity scales, symptom-related scales (e.g. constipation and faecal incontinence) will further guide the healthcare professional to determine the degree of the disordered defecation and to suggest the level of treatment approach.

The available treatment options are usually divided into different levels depending on the complexity and invasiveness of the intervention.

*The first step* consists of diet and fluid recommendations, e.g. increase of dietary fibre and fluid intake, lifestyle alterations, e.g. increase level of physical activity, oral laxatives and constipating drugs, e.g. bulking agents, stool softeners etc. Even though these basic interventions are widely recognized and utilized in the medical and nursing communities the scientific evidence base is remarkably scarce and conflicting. Abdominal massage has been suggested as an accessible route in the treatment of disordered defecation and one study on 30 MS patients reported significant improvement of constipation symptoms in the group that received abdominal massage compared to the control group. However, this finding needs to be confirmed in studies with larger populations of patients with NBD.

*The second step* is based on digital rectal stimulation, suppositories and biofeedback. Digital rectal stimulation is a procedure performed by the insertion of a gloved and lubricated finger into the rectum and anal canal, rotating gently with a circular movement. This procedure activates preserved anorectal reflexes and thus increases motility in the anorectum^20 and the left colon.

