### 3.3 Study Design Rationale

Transanal irrigation of the bowel can be defined as a process of facilitating evacuation of faeces from the rectum and descending colon by passing water into the bowel via the anus. Two recent reviews have suggested that in individuals with chronic NBD, irrigation outperforms more conservative methods, reducing faecal incontinence and constipation, and as a consequence also improves self-reported quality of life. However there is currently lack of evidence identifying robust criteria for suitability, the impact of long term use on colonic function and reason for poor compliance over time. Thus, we have designed an open, prospective, non-controlled, qualitative multicentre study with the primary objective to evaluate the change in NBD score after use of the novel Navina Smart system. The assumption is that the NBD symptoms are constant over time (i.e. 12 months of study duration) if not treated in any way. The hypothesis in the present study is that any change in NBD Score is because of use of the Navina Smart system and hence no control group is required.

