## **5.2 Procedures**

The study device should only be used in this study and according to the Clinical Study Protocol (CSP).

For complete information regarding: preparation, activation, instillation, evacuation, disassembling and cleaning of the Navina Smart system, **see Appendix D; Instructions for use**. The Instructions for use (IFU) provides directions to help users and healthcare professionals to operate the Navina Smart system.

Navina Smart system helps patients with NBD symptoms to empty their bowels. When the catheter is inserted into the rectum, a small balloon fills with air to keep the catheter in place during intestinal irrigation. The balloon also functions as a seal inside the rectum to help retain the water as it is instilled into the bowel.

Process for initiation of the therapy will primarily be based on clinical judgment based on individual prerequisites. It is however recommended that the initiation is very careful to offer the best possible introduction for the patient. **Appendix C; Navina Treatment Schedule**, describes the recommended settings in tailoring and careful monitoring of the therapy to fit individual needs.

Subjects, who start to use Navina Smart, must be motivated and feel confident with the system. It is also essential that the subjects understand what TAI is and the risks involved. This is achieved by thorough information and training, together with proper follow-up and should include the following:

- *Anatomy and physiology of the bowel tract.*
- *The individual patient's bowel dysfunction as compared to normal bowel function.*
- *Information about what TAI is.*
- *TAI technique: hygiene, equipment, catheter insertion, emptying procedure, handling aids.*
- *The importance of regular bowel emptying with a deliberate program.*
- *Information about the risks involved and complications and where to turn to if they appear.*

- *Information on where to find more information concerning the training and training sessions, e.g. homepages, Navina-app, Navina training.*
- *Information about Navina Smart system and how it works.*

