### 7.4 Determination of Sample Size

This study aims to look at change in NBD score (range from 0 (very minor bowel dysfunction) to 47 (severe bowel dysfunction)) after introducing TAI with the Navina Smart system in a population with a common feature of having neurological bowel dysfunction. Each patient serves as his/her own control, by measuring change in NBD score before and after treatment with the Navina Smart system. The NBD score is a validated questionnaire and tool that correlates neurological bowel dysfunction to QoL. In this study a patient friendly version of the NBD Score will be used.

To determine the sample size of the study the following formula is used, referred to in Lachin 1981, considering the fact that a pair wise comparison is made.

$$N = \frac{(Z_{\alpha} + Z_{\beta})^2 \sigma^2}{\mu_1^2}$$

Where:

$\mu_1$  = minimal important difference or difference worth detecting

N = Total number of patients

$Z_{\alpha} = 1.96$  (5% two-sided significance level)

$Z_{\beta} = 1.28$  ( $1-\beta = 0.90$ ), 90% power or 0.84 ( $1-\beta = 0.80$ ), 80% power

$\sigma$  = standard deviation of difference in NBD score between baseline (without Navina™) and 3 months use of Navina™.

The table below shows number of patients needed using different levels of minimal important difference and standard deviations, using 90% power and 5% two-sided significance level.

Total sample size for paired observations where  $\sigma$  is known and defined as standard deviation of difference between baseline and follow-up.

| $\mu 1$    | $\sigma = 2.0$ | $\sigma = 2.1$ | $\sigma = 2.2$ | $\sigma = 2.5$ |
|------------|----------------|----------------|----------------|----------------|
| 0.8 | 66             | 73             | 80             | 103            |
| 1.0 | 43             | 47             | 51             | 66             |
| 1.2 | 30             | 33             | 36             | 46             |
| 1.5 | 19             | 21             | 23             | 30             |
| 2.0 | 11             | 12             | 13             | 17             |
| 2.5 | 7              | 8              | 9              | 11             |

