The chosen minimal important difference for the study is related to the fact that also small difference could be clinically meaningful for the patients. In addition, depending on baseline NBD score level, smaller, but still valid, changes may be present when starting at a level closer to the inclusion cut of 10 than if the starting point is around 14. For this reason we believe a minimal important difference level valuable to detect in the study of ~0.8 would be representative.

Christensen et al describe in their sample published in 2008 a mean difference in NBD score of -4.5 with corresponding 95% confidence interval of -6.6 to -2.4 after introducing TAI for a 10 weeks' period. This indicates that the expected standard deviation for the difference between baseline and follow up in NBD score would lie somewhere around 2.1-2.2. For detection of a minimal important difference of 0.8, with an expected standard deviation of 2.2, a total of 80 (90% power) subjects who has been using Navina Smart for 3 months are required. However, since higher variability than expected and high drop-out rates may risk the final numbers additional patients must be accounted for. For example, Gosselink et al. reported a discontinuation rate of 55% when introducing TAI therapy in their sample reported in 2004 and Christensen et al. observed a discontinuation rate of 45%, why it is recommended to recruit at least 150 patients in the current study. This will allow 70 of 150 (47%) to drop-out from the study with maintained 90% power to detect a difference of 0.8 between a baseline NBD score (without Navina Smart) and after using Navina Smart for 3 months.

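### Any NBD change is attributed to the device on a no-treatment assumption that does not fit subjects whose non-drug bowel care is unrestricted and scheduled for evaluation only at baseline

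*Protocol*

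**What the plan says.** The synopsis (Objectives) takes NBD symptoms as constant over the study and adds that "the hypothesis is that any change should be because of the use of the Navina Smart system". Section 3.3 gives the same argument with a condition attached: "The assumption is that the NBD symptoms are constant over time (i.e. 12 months of study duration) if not treated in any way". From this it concludes that a control group is unnecessary. Each subject serves as his or her own control.

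The Background sets out a treatment ladder for NBD. Its first step includes "diet and fluid recommendations, e.g. increase of dietary fibre and fluid intake, lifestyle alterations, e.g. increase level of physical activity", with abdominal massage also mentioned. Its second step includes digital rectal stimulation and biofeedback. The Background also says that immobility and dietary change contribute to NBD.

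Section 4.4 bars other irrigation systems, prokinetics, anticoagulants, long-term systemic steroids and newly started opioids, and asks that laxative use stay unchanged. It has no entry for the non-drug methods.

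The training list in Section 5.2 covers the device and irrigation technique, but also bowel anatomy and function and "The importance of regular bowel emptying with a deliberate program".

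Current bowel care has its own row in Table 3, marked at Visit 1 only. Section 6.4.3 agrees: the Baseline Questionnaire, which measures current bowel management, "is self-administrated and will be completed by each subject only at Baseline (Visit 1".

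**The concern.** The constancy assumption concerns people who receive no treatment. The comparison actually made is conservative care before Visit 1 against irrigation plus whatever conservative care continues, is added or is dropped afterwards, following a training session that goes beyond the device. Constant symptoms without treatment, even if true, would not make that difference a device effect.

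The attribution matters because the protocol uses it to dispense with a control group and because the study is meant to show professionals and users that the product is effective (Section 1.1). If non-drug care shifts after Visit 1, the shift enters the primary result. No described data item would show that it had happened.

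**Working it through.** **1. The plan's own figure.** Section 7.4 works with a "5% two-sided significance level" (Z = 1.96), 90% power (Z = 1.28), an SD of the paired difference of 2.2 and a difference of 0.8.

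N = (1.96 + 1.28)² × 2.2² / 0.8² = 10.4976 × 4.84 / 0.64 = 79.39, rounded up to 80.

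This reproduces the stated 80. The allowance of 70 drop-outs from 150 (70/150 = 46.7%) leaves 80, as stated. The sample-size arithmetic is not at issue here.

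**2. What is controlled and what is recorded after Visit 1.**

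| Element of bowel care | Rule in Section 4.4 | Follow-up record described |
|---|---|---|
| Laxatives | Kept unchanged | Yes: medication during the study (Section 6.1), changes noted at Visits 2 and 3 (Section 3.2) |
| Prokinetics, new opioids | Not allowed | Yes, as medication |
| Other irrigation systems | Not allowed | Not needed for this point |
| Diet, fluids, physical activity | None | None described |
| Abdominal massage, digital stimulation, biofeedback | None | None described |

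The Background describes suppositories and micro-enemas as forms of mild laxative, so they are counted here as drug care. The last two rows are the gap. Section 6.4.4 says the Follow-up Questionnaire covers perception and satisfaction, five device dimensions, compliance, UTI and healthcare use; its items are not shown. Section 7.1.2 promises to examine covariates, but for non-drug care no post-baseline data are described.

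**3. Why a small shift would matter (illustration).** The documents give no size for a non-device change, so the shifts below are assumptions, with the device effect set to zero. A normal approximation to the paired test is used; the planned test is the Wilcoxon signed rank test.

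- Smallest significant mean change = 1.96 × σ/√N. For σ = 2.2 and N = 80: 1.96 × 2.2/8.944 = 0.48.
- Probability of p < 0.05 = Φ(δ√N/σ − 1.96) + Φ(−δ√N/σ − 1.96). For δ = 0.4, σ = 2.2 and N = 80: δ√N/σ = 1.626, and the probability is 36.9%.

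| SD | N | Smallest significant mean change | Shift 0.2 | 0.4 | 0.6 | 0.8 |
|---|---|---|---|---|---|---|
| 2.2 | 80 | 0.48 | 12.8% | 36.9% | 68.4% | 90.2% |
| 2.2 | 150 | 0.35 | 20.0% | 60.5% | 91.6% | 99.4% |
| 4 | 80 | 0.88 | 7.3% | 14.5% | 26.9% | 43.2% |
| 4 | 150 | 0.64 | 9.4% | 23.2% | 45.1% | 68.8% |
| 6 | 80 | 1.31 | 6.0% | 9.2% | 14.5% | 22.2% |
| 6 | 150 | 0.96 | 6.9% | 12.9% | 23.2% | 37.2% |

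Only the SD of 2.2 comes from the protocol; 4 and 6 show how far the illustration depends on it. In every row the test responds to change from baseline, whatever its source.

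**The case against.** The best defence has four parts.

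- *The wording is a hypothesis, not a finding.* The protocol labels it so. That stands, but Section 3.3 draws a design conclusion from it, and no later section limits the claim.
- *Training and support belong to irrigation therapy.* Section 5.2 treats them as essential to starting safely and confidently. That is fair, and it is the reason to name the whole package as the thing evaluated. It does not support attribution to the device.
- *The room for confounding is limited.* Inclusion criterion 7 requires that conservative therapy has already failed, laxatives are held stable, and the Background calls the evidence for first-step measures scarce and conflicting and biofeedback better suited to milder cases. All of this reduces the problem without removing it.
- *A real effect may dwarf it.* The cited 2008 study reports a mean change of −4.5. A shift of 0.48 is 0.48/4.5 = 11% of that. If the observed change were that large, modest co-intervention would not explain it. The protocol, however, builds the study on a difference of 0.8 and attributes any change to the device.

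Two stronger readings are tempting and should be resisted. A reader might infer that the weekly calls alter conservative care. Sections 3.2, 5.2 and 5.3 confine the advice to the irrigation regime, so the calls add contact and support but are not shown to change other bowel care. A reader might also infer that no later check is possible. The Follow-up Questionnaire items are not shown, and Table 6 draws perception of bowel management from both questionnaires, so some capture cannot be excluded. What can be said is that none is described.

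**Conclusion.** The concern holds in this form: attributing any NBD change to the device, and inferring that no control group is needed, is not supported, because the no-treatment assumption does not describe the own-control comparison. Non-drug conservative care is unrestricted after Visit 1, its scheduled evaluation is at baseline only, and the training may alter it.

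The size is unknown. The documents give neither the amount nor the direction of a non-device shift; dropping a conservative method could raise the score. The figures above show only that, at the planning SD of 2.2, a mean change of 0.48 points (N = 80) or 0.35 points (N = 150) from any source is significant. At larger SDs the threshold rises.

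A reader might go further and infer that the single-arm design is itself an error or that a particular share of the effect is spurious. Neither follows. Sections 1.1 and 3.3 also justify a single arm by the CE-marking, and a change from baseline remains a valid thing to report. What needs correcting is the claim attached to it.

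**What to change.** 1. In the synopsis and Section 3.3, replace the attribution with: *change from baseline after TAI with Navina Smart, delivered with structured training and telephone support, on continuing conservative care*. Delete the inference about the control group, and state that the single-arm design cannot separate the device from these accompanying elements.
2. Repeat the current-bowel-management items of the Baseline Questionnaire at Visits 2 and 3, and mark those columns in the Table 3 row on current bowel care.
3. Report changes in conservative care descriptively. Do not split the primary result by methods kept, added or dropped in order to claim a device effect. This is a post-baseline variable that irrigation may itself change: good responders may drop digital stimulation because irrigation works, and poor responders may add methods. The split could not remove training or contact either, since every subject receives them.

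The cost is a few existing questions asked twice more, a Table 3 edit and a narrower claim. No sample-size figure changes, and no clinical rule on bowel care is needed.
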